### Objectives

#### Primary objective

To evaluate the feasibility, safety, and preliminary efficacy of combined iTBS and individualized tSCS, delivered with standardized upper limb rehabilitation, compared with tSCS and rehabilitation alone, for improving upper limb motor function in adults with chronic incomplete cervical SCI.

#### Secondary objectives

1. To assess the effects of adjunctive iTBS on UE functional capacity, independence in activities of daily living, and health-related quality of life.

2. To characterize the neurophysiological effects of combined stimulation on corticospinal excitability, including central motor conduction time and motor evoked potential parameters.

3. To evaluate the safety and tolerability of the combined intervention.

4. To determine the durability of treatment effects at 4- and 12-week follow-up.

5. To generate effect size estimates and feasibility data to inform the design of a subsequent adequately powered multicenter confirmatory trial.

#### Hypotheses

We hypothesize that participants receiving adjunctive iTBS will demonstrate (1) a clinically meaningful additional improvement of 2 or more points in UEMS compared with tSCS-based rehabilitation alone, and (2) enhanced corticospinal tract plasticity, as reflected by neurophysiological measures, with functional gains maintained at follow-up. A 2-point UEMS change approximates the minimal clinically important difference in chronic cervical SCI, reflecting gain of at least one muscle grade in a key upper limb muscle and typically corresponding to a functional gain such as independent self-feeding or grooming.

## Methods

### Trial design

This is a single-center, two-arm, parallel-group, assessor-blinded, pilot randomized controlled trial. The protocol has been developed in accordance with the Standard Protocol Items: Recommendations for Interventional Trials (SPIRIT) 2013 statement (Chan et al., 2013), the SPIRIT-iNeurostim extension for neurostimulation trials (Bresnahan et al., 2024), and the CONSORT 2010 extension for pilot and feasibility trials (Eldridge et al., 2016). The trial will be prospectively registered on ClinicalTrials.gov prior to enrollment of the first participant. This protocol is reported according to JMIR Research Protocols guidelines for protocol papers.

### Ethical considerations

This protocol will be submitted for approval to the National Healthcare Group Domain Specific Review Board (NHG DSRB), which serves as the ethics committee for studies conducted at Alexandra Hospital under the National University Health System (NUHS). All participants will provide written informed consent following a comprehensive explanation of the study procedures, risks, potential benefits, and alternatives. The informed consent process will include verification of participant understanding using a teach-back method. Participants will be free to withdraw at any time without affecting their standard clinical care. The study will be conducted in accordance with the Declaration of Helsinki (2013 revision), the International Council for Harmonization Good Clinical Practice (ICH-GCP) guidelines, and Singapore’s Human Biomedical Research Act (HBRA).

### Study setting

The trial will be conducted at the. Alexandra Hospital is a public general and rehabilitation hospital that provides comprehensive inpatient and outpatient SCI rehabilitation services under the NUHS cluster. All study interventions and assessments will take place in a dedicated neuromodulation research suite within the rehabilitation department.

### Eligibility criteria

The inclusion and exclusion criteria are summarized in Table 1.

**TABLE 1 T1:** Eligibility criteria.

Inclusion criteria	
**Age**	21–65 years
**Chronicity**	More than 12 months post-injury at enrollment
**Injury type**	Traumatic or non-traumatic incomplete cervical SCI, neurological level C2 to C8
**AIS classification**	Grade C or D
**UEMS**	10 to 20 out of 25 on the more impaired side; lower bound 10 ensures sufficient voluntary activation for task training and elicitable MEPs, upper bound avoids ceiling effects.
**Grip strength**	MMT grade 3 or higher in finger flexors (C8 myotome) on at least one side.
**Hand function**	Able to transfer at least 1 block across the partition within 60 s on the more impaired side.
**Sitting tolerance**	Able to tolerate upright seated posture in own wheelchair for at least 1 continuous hour without symptomatic orthostatic hypotension or pressure-related discomfort requiring position change.
**Medical stability**	No acute medical complications
**Informed consent**	Able to provide written informed consent and comply with the study schedule
**Medications**	Stable regimen for 4 weeks prior, AND participant plus clinician agreement that dosage (baclofen, tizanidine, botulinum toxin) remains unchanged throughout the 12-week intervention; any change logged as protocol deviation
**Surgical clearance**	Cleared by neurosurgeon or orthopedic surgeon for participation in tSCS-based rehabilitation
Exclusion criteria	
**Seizure history**	History of seizures or epilepsy
**Implanted devices**	Intracranial metallic implants, cochlear implants, cardiac pacemakers, or other implanted electronic devices. Cervical spinal instrumentation (e.g., posterior rods, plates, or screws at C2 to T1) is not an exclusion for tSCS provided overlying skin is intact; participants with hardware directly beneath planned electrode sites will undergo low-intensity test stimulation during screening, and electrode placement will be shifted by one interspace if current distortion, focal discomfort, or unexpected motor thresholds are observed. Intracranial hardware remains an absolute exclusion for iTBS.
**Prior craniotomy**	Prior neurosurgical procedure involving craniotomy
**Pregnancy**	Currently pregnant or intending to become pregnant during the study period
**Psychiatric or cognitive**	Active psychiatric illness (eg, untreated major depression, psychosis) or cognitive impairment precluding informed consent
**Concurrent neurological disease**	Progressive or degenerative neurological condition (eg, multiple sclerosis, motor neuron disease)
**Concurrent trials**	Participation in another interventional rehabilitation or neurostimulation trial
**Skin integrity**	Skin lesions or breakdown at electrode placement sites (scalp or posterior cervical spine)
**Cortical excitability medications**	Medications known to alter cortical excitability (eg, antiepileptic drugs, high-dose benzodiazepines) that cannot be stabilized for at least 2 weeks prior to enrollment
**Severe spasticity**	Modified Tardieu Scale muscle reaction grade 4 (unfatigable clonus > 10 s) at elbow or wrist flexors on the more impaired side, or spasticity judged by the treating physician as unresponsive to optimized pharmacological management.

AIS, American Spinal Injury Association Impairment Scale; UEMS, Upper Extremity Motor Score; SCI, spinal cord injury; tSCS, transcutaneous spinal cord stimulation.

Restriction to motor-incomplete injuries is mechanistic. Convergent neuromodulation relies on residual corticospinal substrate for STDP-driven strengthening; AIS A and motor-absent AIS B injuries cannot reliably engage this pathway and would produce UEMS floor effects. Extension to AIS B participants with preserved transcranial MEPs is planned for the confirmatory trial.

### Recruitment and retention

Participants will be recruited from the outpatient SCI clinic and inpatient rehabilitation ward at Alexandra Hospital and National University Hospital, as well as through the SCI patient registry maintained by the NUHS rehabilitation service, community SCI support organizations (e.g., SPD, Singapore), and social media advertisements. Strategies to optimize recruitment and reduce dropout include flexible scheduling of treatment sessions, provision of make-up sessions for missed appointments (up to 2 per month), reimbursement of travel expenses, and regular communication with participants regarding study progress. A recruitment rate of 2–3 participants per month is anticipated based on institutional patient volumes.

### Randomization and allocation concealment

Participants will be randomized in a 1:1 ratio using a computer-generated, permuted block randomization schedule (block sizes of 4 and 6, randomly varied) stratified by AIS grade (C versus D) and baseline UEMS on the more impaired side (10–14 versus 15–20). The randomization schedule will be generated by an independent biostatistician at the Clinical Research & Innovation Office, Tan Tock Seng Hospital, with no direct involvement in participant recruitment or assessment, and stored in a secure, web-based centralized randomization system (REDCap Randomization module). Allocation concealment will be ensured by sequential, opaque, sealed envelopes accessible only to the unblinded intervention therapist.

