### Blinding

This trial employs an assessor-blinded design in which outcome assessors are blinded to treatment allocation. A dedicated, unblinded intervention therapist will be responsible for delivering iTBS and configuring tSCS at each session and will have no involvement in outcome assessment. Participants in the control arm will be aware that they are not receiving iTBS, as the brief nature of the iTBS procedure and the characteristic scalp sensation make participant-level sham impractical in this pilot study. To mitigate expectation effects, both arms will be framed during consent as “active neuromodulation combined with rehabilitation” with no comparative ranking. Both groups receive identical therapist contact time, session structure, and rehabilitation content. The Credibility/Expectancy Questionnaire will be administered at baseline and week 2 and entered as a covariate in sensitivity analyses of the primary outcome. However, assessor blinding will be rigorously maintained through physical separation of intervention delivery and outcome assessment areas within the rehabilitation department. The success of assessor blinding will be formally evaluated using a blinding questionnaire at week 12 and week 24. Bang’s Blinding Index will be used, a validated metric ranging from minus 1 (opposite guessing) to +1 (complete unblinding), with 0 indicating random guessing. If Bang’s Blinding Index exceeds 0.2 with 95% CI excluding zero, a pre-planned sensitivity analysis will re-analyze the primary outcome using only objective/instrumented measures (grip/pinch dynamometry, Nine-Hole Peg Test, Box and Block Test, and neurophysiological parameters), and an independent second assessor will re-score a random 30% sample of ISNCSCI examinations from video recordings.

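### Two allocation routes are named without saying which governs, and the one given the job of concealment leaves upcoming assignments in the sole custody of the treating therapist

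*Protocol article*

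**What the plan says.** All the relevant text is in two sections of the protocol article.

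- **Randomization and allocation concealment, generation and storage.** An independent biostatistician, described as "with no direct involvement in participant recruitment or assessment", generates the schedule, which is then "stored in a secure, web-based centralized randomization system (REDCap Randomization module").
- **Same section, concealment.** The next sentence gives this job to a different device: "Allocation concealment will be ensured by sequential, opaque, sealed envelopes accessible only to the unblinded intervention therapist".
- **Same section, structure of the schedule.** Allocation is 1:1 in permuted blocks, each of size 4 or 6 chosen at random. The list has four strata, being "stratified by AIS grade (C versus D) and baseline UEMS on the more impaired side (10–14 versus 15–20").
- **Blinding.** "A dedicated, unblinded intervention therapist will be responsible for delivering iTBS and configuring tSCS at each session". This person "will have no involvement in outcome assessment". Control participants know that they receive no iTBS.

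The article does not say how the REDCap list and the envelopes relate, or which one produces the binding assignment.

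**The concern.** Concealment protects the period before allocation: who is approached, who is judged eligible, and when each person is entered. It works best when nobody near that process holds the next assignment. The plan has a central system that can do this, yet it gives concealment to paper held on site by one person. That person learns the arm of each participant treated and is the only one described as having access to the envelopes.

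If that person also influenced enrolment or its timing, the two arms could differ systematically at entry. Assessor blinding acts after allocation and cannot correct this. The primary model adjusts for AIS grade and baseline UEMS, so it would at least partly handle selection on those two factors, but not on unrecorded prognosis or motivation. With 12 participants per arm, a few selectively timed entries could move the UEMS contrast, and that effect-size estimate is meant to inform the confirmatory trial.

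**Working it through.** The plan gives no figure on this point, so there is nothing to reproduce. The check compares the statements with one another, and then asks whether any number measures the weakness.

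**1. Which route governs?** Storage is assigned to REDCap and concealment to envelopes, in consecutive sentences. They could be one workflow, in which the list is stored centrally and printed into envelopes. They could also be two parallel routes. The text does not settle it.

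**2. Who is kept away from what?**

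| Role | Stated separation |
|---|---|
| Biostatistician who generates the schedule | Recruitment and assessment |
| Therapist who holds the envelopes | Outcome assessment only |

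The separation from recruitment, which is what concealment needs, is stated for the biostatistician but not for the person with custody of the assignments.

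**3. Does the visit schedule close the gap?** Table 3 places consent, eligibility and surgeon clearance at Screen and randomization at Baseline. Stratifying on baseline UEMS also means that this score must be known before assignment. This orders the steps for each participant. It does not determine who holds the assignments for later participants.

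**4. Can the weakness be sized by predictability?**

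*Inputs from the article:* N = 24, ratio 1:1, blocks of 4 and 6, and 2 × 2 = 4 strata. *Assumptions:* the two block sizes are equally likely, and the spread of participants over strata is varied because the article does not give it.

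*One step by hand:* the first allocation in a stratum is a 50/50 guess. If it is arm A, the chance that the second is arm B is

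½ × 2/3 + ½ × 3/5 = 0.333 + 0.300 = 0.633.

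*Whole trial:* 20,000 simulated trials, with an observer who knows every earlier allocation in the stratum and the possible block sizes, and who predicts the next allocation by Bayes' rule.

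| Spread over strata | Correct guesses | Next allocation certain | Probability at least 0.75 |
|---|---|---|---|
| Four equal strata | 65.8% | 5.5% | 36% |
| 40/30/20/10 | 65.7% | 5.2% | 36% |
| All in one stratum | 68.7% | 5.8% | 46% |
| By chance | 50% | – | – |

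These figures use only the block structure and knowledge of past arms. Envelopes do not enter the calculation, so removing them leaves every entry unchanged. The table describes a background property of a blocked, open-label trial and does not measure the custody arrangement.

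**The case against.** The strongest reply has five parts.

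- **Custody is not knowledge.** Opaque, sealed envelopes used in sequence are a recognised method, designed so that the holder cannot see the next assignment. *This stands.* A reader might infer that the therapist can see upcoming allocations, so that prediction reaches 100%. That requires seals to be broken or bypassed, and nothing in the article suggests it.
- **No enrolment role is documented.** Selection bias needs someone who both foresees the allocation and influences entry. The article describes recruitment through clinics, wards, a registry, community organizations and social media, and much of eligibility rests on measured criteria and surgical clearance. *This stands.* A reader might infer that the therapist screens or recruits. The text does not say so, and in a condensed article its silence on staff delegation would not be a finding by itself.
- **The guessing rate is not about envelopes.** *This stands in full,* as the working shows.
- **The two sentences may describe one workflow.** Restricting access to the one person who must know the arm also helps assessor blinding. *This stands in part.* The text can be read that way, so it is unclear rather than contradictory. It still assigns concealment to the on-site paper copy.
- **The trial is an exploratory pilot.** *True, but of limited weight.* Its effect estimates are intended to inform the next trial.

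What the reply does not remove is the explicit choice of custodian. The article itself states who alone has access to the envelopes, and a stronger mechanism is named one sentence earlier.

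**Conclusion.** The point holds as an avoidable weakness in the stated procedure. The article names two allocation routes without saying which governs. It relies for concealment on the weaker one, with future assignments on site in the sole custody of someone who knows earlier allocations and is stated to be separate from outcome assessment only.

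This leaves a risk of selection bias open and does not demonstrate any. Realised harm would need two things that the article does not report: foreknowledge or a good guess of the next allocation, and influence over who is entered or when. No figure for its size is justified. The 66% (69% if all participants fall in one stratum) rests on the assumed block-size probabilities and stratum spread and would persist after the change. The 100% presupposes failed seals. The case for acting is that the better mechanism is already named in the plan, and that bias introduced before allocation cannot be reliably repaired in the analysis.

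**What to change.** Amend the section Randomization and allocation concealment in three respects.

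1. Make the REDCap Randomization module the only route of assignment. It should release each allocation singly, after consent, eligibility and the AIS and baseline UEMS stratum have been recorded.
2. Drop the envelopes. If a fallback is wanted, have a party independent of both treatment and recruitment hold them, with every use logged.
3. State that the intervention therapist takes no part in recruitment or eligibility decisions. This clause also limits the harm from the residual guessing, which the first two changes do not affect.

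**Cost.** A few sentences in the protocol. REDCap is already planned, and the Results section says that no participant had been enrolled when the manuscript was prepared. The small downside is dependence on system access at the time of randomization, which the logged backup would cover. Sample size, strata, block sizes and analysis need not change.

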### Blinding

This trial employs an assessor-blinded design in which outcome assessors are blinded to treatment allocation. A dedicated, unblinded intervention therapist will be responsible for delivering iTBS and configuring tSCS at each session and will have no involvement in outcome assessment. Participants in the control arm will be aware that they are not receiving iTBS, as the brief nature of the iTBS procedure and the characteristic scalp sensation make participant-level sham impractical in this pilot study. To mitigate expectation effects, both arms will be framed during consent as “active neuromodulation combined with rehabilitation” with no comparative ranking. Both groups receive identical therapist contact time, session structure, and rehabilitation content. The Credibility/Expectancy Questionnaire will be administered at baseline and week 2 and entered as a covariate in sensitivity analyses of the primary outcome. However, assessor blinding will be rigorously maintained through physical separation of intervention delivery and outcome assessment areas within the rehabilitation department. The success of assessor blinding will be formally evaluated using a blinding questionnaire at week 12 and week 24. Bang’s Blinding Index will be used, a validated metric ranging from minus 1 (opposite guessing) to +1 (complete unblinding), with 0 indicating random guessing. If Bang’s Blinding Index exceeds 0.2 with 95% CI excluding zero, a pre-planned sensitivity analysis will re-analyze the primary outcome using only objective/instrumented measures (grip/pinch dynamometry, Nine-Hole Peg Test, Box and Block Test, and neurophysiological parameters), and an independent second assessor will re-score a random 30% sample of ISNCSCI examinations from video recordings.

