### Interventions

#### Overview

Both arms will receive individualized tSCS combined with standardized upper limb rehabilitation. The experimental arm will additionally receive iTBS immediately prior to each rehabilitation session. Interventions will be delivered twice per week for 12 weeks, yielding a total of 24 sessions. A minimum of 20 completed sessions (83%) will be required for per-protocol analysis.

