#### Standardized upper limb rehabilitation (both arms)

All participants will receive individualized, standardized upper limb rehabilitation during each session, commencing after iTBS delivery (in the experimental arm) and continuing throughout tSCS application. The rehabilitation program is based on the functional task practice protocol employed in the Up-LIFT trial (Moritz et al., 2024) and will be prescribed and supervised by a qualified physiotherapist and occupational therapist at Alexandra Hospital. Each session will comprise approximately 45–60 min of structured UE exercises, including the following components: (1) upper limb ergometry and gross UE movements (reaching, overhead press); (2) isolated finger movements and fine motor tasks; (3) simple and complex pinch tasks using graded objects; (4) grip strength training; (5) bimanual coordination tasks; and (6) individualized functional activities prescribed by the attending occupational therapist based on their clinical assessment. Task difficulty will be adjusted according to the participant’s functional capacity using a standardized progression algorithm.

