#### Treatment session sequence

Each session in the experimental arm will follow the sequence: (1) iTBS over M1 (approximately 3–4 min); (2) tSCS electrode placement and activation (approximately 5 min setup); (3) combined tSCS plus upper limb rehabilitation (approximately 45–60 min). Total session duration for the experimental arm is approximately 55–70 min. The control arm follows the same sequence without the iTBS component, with total session duration of approximately 50–65 min.

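### The Blinding section claims identical therapist contact time and session structure, but the session sequence gives the experimental arm an extra therapist-delivered step of about 3–5 minutes at every session

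*Protocol article*

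**What the plan says.** The Blinding section explains that no sham is used: "Participants in the control arm will be aware that they are not receiving iTBS". The next sentence opens with "To mitigate expectation effects, both arms will be framed during consent as" and describes a neutral presentation of both arms. Directly after it comes the unqualified statement "Both groups receive identical therapist contact time, session structure, and rehabilitation content". The Credibility/Expectancy Questionnaire and its use as a covariate follow. Equal contact is therefore presented as one of a group of measures against expectation effects.

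The same section says who gives the iTBS: "A dedicated, unblinded intervention therapist will be responsible for delivering iTBS and configuring tSCS at each session".

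The intervention sections describe the sessions differently. Overview: "The experimental arm will additionally receive iTBS immediately prior to each rehabilitation session". Treatment session sequence, for the experimental arm: "Total session duration for the experimental arm is approximately 55–70 min". For the control arm: "The control arm follows the same sequence without the iTBS component, with total session duration of approximately 50–65 min". Neither section describes a time-matched activity that replaces iTBS for controls.

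**The concern.** An unqualified statement about bias control disagrees with the article's own description of the sessions. The comparison is open to participants, and the primary outcome, UEMS, is graded muscle strength that depends on voluntary effort, as do the grip, pinch and dexterity tests. Assessor blinding does not act on the participant's own effort or expectation. In that setting, readers give weight to a statement that attention was the same in both arms.

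If a results paper repeats the sentence, it will claim an attention control that the trial did not have. The Limitations section acknowledges possible performance bias because experimental participants know they receive iTBS, but it does not mention that they also have more therapist contact. The pilot's effect sizes are meant to inform a confirmatory trial, so the difference should be visible to whoever uses them.

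**Working it through.** **Inputs**
- iTBS: about 3–4 min per session, experimental arm only (iTBS protocol; Treatment session sequence).
- tSCS setup: about 5 min, both arms (Treatment session sequence).
- tSCS with rehabilitation: about 45–60 min, both arms (Treatment session sequence).
- Sessions: 2 per week × 12 weeks = 24 (Overview).
- Stated totals: experimental about 55–70 min, control about 50–65 min (Treatment session sequence).

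**Reproducing the stated figures**
- iTBS pulses: 20 trains × 10 bursts (2 s at 5 Hz) × 3 pulses = 600. Duration: 19 × 10 s + 2 s = 192 s, in line with 3–4 min.
- Control session: 5 + 45 = 50 min to 5 + 60 = 65 min. This matches the stated range exactly.
- Experimental session: 3 + 5 + 45 = 53 min to 4 + 5 + 60 = 69 min. The stated 55–70 min agrees once rounded to 5 min.

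**Excess contact in the experimental arm**

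| Basis | Per session | Share of a control session | Over 24 sessions |
|---|---|---|---|
| Itemised components | 3–4 min | 3/65 = 4.6% to 4/50 = 8.0% | 72–96 min = 1.2–1.6 h |
| Stated totals (55 − 50; 70 − 65) | 5 min | 5/65 = 7.7% to 5/50 = 10% | 120 min = 2.0 h |

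By the stated totals, contact over the whole course is 22–28 h in the experimental arm (24 × 55/60 to 24 × 70/60) and 20–26 h in the control arm (24 × 50/60 to 24 × 65/60). Identical contact would need an excess of zero, and neither basis gives that.

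**Structure**

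The experimental session has three steps: iTBS, tSCS setup, then tSCS with rehabilitation. The control session has the last two only.

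**Content**

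The rehabilitation section gives all participants the same six components, the same 45–60 min and one progression algorithm. Nothing there separates the arms.

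**The case against.** The best defence is that contact time means the rehabilitation block, which is equal. That reading does not save the sentence. The Blinding section itself assigns iTBS to the intervention therapist, so those minutes are therapist contact, and a session with one step fewer does not have an identical structure.

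Other points on that side do stand:
- The gap is small. It is well below the 15 min spread allowed within either arm, and the matched part is over 90% of an experimental session (50/55 = 91% at the short end, 65/70 = 93% at the long end).
- The unequal durations are printed openly in the Treatment session sequence section.
- Expectation arises mainly because participants know their arm. A few attended minutes for controls would not remove it.
- All efficacy comparisons are declared exploratory.
- The Introduction already commits the trial to capturing setup time and therapist burden, so part of the remedy is planned.

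A reader might infer two further faults that the article does not support:
- One is that content also differs, because sessions include "individualized functional activities prescribed by the attending occupational therapist based on their clinical assessment". That tailoring applies to participants in both arms and is not a difference between them.
- The other is that finding the motor hotspot and active motor threshold makes the gap larger. The article gives neither the duration nor the frequency of that work at treatment visits, and motor thresholds are outcomes measured in both arms at the assessment visits. Any addition is conditional and cannot be sized.

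**Conclusion.** The point holds for contact time and session structure. The experimental arm has 3–4 min more therapist contact per session by components, or 5 min by the approximate totals, with no substitute for controls. This rests on two assumptions: that iTBS delivered by the therapist counts as therapist contact, and that the approximate durations are those intended in practice.

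It would go too far to conclude that the trial has no protection against expectation effects. The neutral consent framing, the expectancy covariate and assessor blinding are untouched, and the tSCS setup, rehabilitation time and rehabilitation content are matched. Nor does the article give grounds to say that a few extra minutes would by themselves move UEMS. What fails is one stated property of the design, which should be corrected before it is relied on or repeated in the results. No participants had been enrolled when the article was prepared, so the correction can be made in time.

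**What to change.** Reconcile the Blinding and Treatment session sequence sections:
1. Limit the Blinding sentence to what is matched: tSCS setup, and rehabilitation time and content.
2. State there that the experimental arm has an additional therapist-delivered iTBS step at each session, and give its approximate length.
3. Add the unequal contact to the performance-bias item in the Limitations section.
4. Use the time capture already planned in the Introduction to report therapist minutes and rehabilitation minutes per session by arm.

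The cost is a few sentences and a minor addition to reporting. An attended period of equal length in the control arm would make the contact-time claim true, but it is an optional design preference. At 5 min per session it would take 24 × 5 = 120 min, or 2 h, of therapist time per control participant.
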